**Recruitment of participants**

i. Site PIs (cardiologists) and cardiology nurses and cardiology pharmacists will identify potential study participants. Cardiologists, cardiology nurses and cardiology pharmacists have been briefed about this study and they are aware of the inclusion/exclusion criteria. They have been requested to refer patients whom they are seeing in their clinics and pharmacies to the study team. As a reminder of the study, all clinicians will have a clinician flyer which will be put up at a spot where they can see it. At this stage of the recruitment process, the study team will not have any access to potential study participants.

ii. During the referral process, site PIs (cardiologists) and cardiology nurses and cardiology pharmacists doing the referral will brief their patients about this study and provide them with a study flyer. Details of potential participants will be provided to the research team by the referring clinicians via email. The email by the clinician will also give permission to the research team to have access to the potential participants medical records should they give informed consent to participate in the study.

iii. A member of the research team will contact potential participants referred to them by the clinicians one week later for an initial interview. At this initial interview, the member of the research team will screen the potential participant for eligibility and then obtain informed consent from those who agree to participate in the study. This contact will be in the form of phone call, via skype (mainly for the rural patients) or face to face if the potential study participant is coming into the clinic for one of their routine follow ups.

iv. Only after getting informed consent from study participants will the member of the research team conduct a baseline assessment which will also consists of getting clinical data from the patient’s medical records.

**Randomisation and blinding**

Participants will be randomly allocated in a 1:1 ratio to either intervention or control group arms. Randomising of study participants will be done according to the random number generator from <https://www.random.org/integers/?num=220&min=1&max=220&col=5&base=10&format=html&rnd=new>. Participants allocated even numbers will be cases and participants allocated odd numbers will be controls. Participants randomized in the control arm will be blinded to the intervention. Due to the nature of the intervention, it will not be possible to blind the investigators. However, to minimize bias, all participants will be allocated a study ID and all data will be collated using the study ID. Analysis of the data will be conducted by blinded investigators.

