**Setting**

The study will be conducted in six investigator centres in South Australia: five South Australian metropolitan hospitals (Royal Adelaide Hospital, Queen Elizabeth Hospital, Lyell McEwin Hospital, Flinders Medical Centre and Noarlunga Hospital) and rural patients will be recruited from integrated Cardiovascular Clinical Network (ICCNet). A total of 220 patients will be recruited and randomized to either the intervention arm or control arm of the study. Eligible participants will be briefed about the study by the treating physician or nurse and they would then be referred to a member of the research team either in person or by skype call when participants come into the hospital for their regular outpatient clinic visits, when the community cardiac nursing team visit patients at home or, in the case of rural patients, during their scheduled skype ‘visit’ with cardiac nurses. Potential participants will be provided with a summary study information and will be contacted by the research team for an initial face-to-face interview either at any of the participating hospitals or via skype for rural patients. At this initial visit, after screening for eligibility, written informed consent will be obtained from those who agree to participate in the study and a baseline assessment will be completed by a member of the research team. A record of non-participation will be kept for those who are ineligible or those who decline to participate in the study. Follow ups at months 3, 6 and 9 will be conducted over phone or skype by a member of the research team.

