**Sample size**

Sample size calculations are focused on two different measures and were also done assuming equal numbers of participants in each group. The first measure takes into account an absolute increase in mean adherence of 15 % (Hulley et al., 2013). In this measure, at two tailed 0.05 significance level with a power of 80 % and standard deviation of 35 (Goldstein et al 2014), the number of participants required in each group is 86. In the second measure, the analysis is by comparing proportions of adherence (Hulley et al., 2013). Previous studies have estimated the adherence to cardiovascular drugs to be up to 60 % (Chowdhury et al., 2013; Bowry et al., 2010). In this measure, a total sample size of 182 participants is needed to provide 80 % power to detect an increase in the proportion of adherent participants from 60 % to 80 %, with a two tailed 0.05 significance level. Therefore, taking the larger of the two sample sizes (91 participants in each arm), and allowing for a 20 % loss to follow up, a total of 220 participants will be recruited in this study with each arm consisting of 110 participants.

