In charge of all daily activities related to the clinical trial, including liaising with the different site clinicians who will be referring patients to her for recruitment, recruitment of all study participants, familiarising participants in the interventional arm to the NPS MedicineWise application, liaising with NPS MedicineWise staff and pharmacists who will be doing intervention tiers 2, 3 and 3A, all follow ups with study participants at baseline, months 3, 6 and 9, and economic analysis. Complete the requirements of a masters program at University of South Australia.

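### The allocation method defines no fixed list and no concealment step, so nothing in the protocol prevents the recruiter from foreseeing or redrawing the next assignment

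*Protocol*

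**What the plan says.** Under Randomisation and blinding, the Protocol states the ratio: "Participants will be randomly allocated in a 1:1 ratio to either intervention or control group arms". The numbers come from a web link, "https://www.random.org/integers/?num=220&min=1&max=220&col=5&base=10&format=html&rnd=new", and the rule applied to them is: "Participants allocated even numbers will be cases and participants allocated odd numbers will be controls". The same section adds: "Due to the nature of the intervention, it will not be possible to blind the investigators". The safeguards it names are study IDs and analysis by blinded investigators.

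Under Sample size: "a total of 220 participants will be recruited in this study with each arm consisting of 110 participants". Under Setting: "The study will be conducted in six investigator centres in South Australia"; one of the six is a rural network reached mainly by Skype.

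Under Recruitment of participants, step iii, at the first interview "the member of the research team will screen the potential participant for eligibility and then obtain informed consent". Step iv places the baseline assessment after consent. The role description after the reference list gives one member of the research team "recruitment of all study participants, familiarising participants in the interventional arm to the NPS MedicineWise application", together with all follow-ups and the economic analysis. The Design section says that those who collect data are not blinded. Under Outcome measures, the primary outcome is a self-reported scale (SEAMS).

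**The concern.** Concealment means that whoever decides on a patient's entry cannot know or influence the arm until entry is settled. Here the recruiter is also the trainer and the follow-up interviewer. Several entry criteria call for judgement: whether the condition is stable, whether email and Skype access is adequate, and whether the patient can follow the study information. A person who knew the next number, or could draw another, could steer entry without breaking a written rule.

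The result would be arms that differ at baseline in motivation or ease with a phone, both plausibly related to self-reported adherence. No analysis reliably repairs that. It is also not a matter for a statistical analysis plan: sequence generation and concealment are trial conduct and must be settled before the first participant.

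**Working it through.** **1. The plan's own arm size.** Inputs from Sample size: difference 15, SD 35; 60% against 80%; two-sided 0.05; 80% power; 20% loss.
- Means: 2 × (1.960 + 0.842)² × 35² / 15² = 85.5, so 86 per arm, as stated.
- Proportions: 91 per arm with continuity correction (82 without), as stated.
- Loss: 91 × 1.2 = 109.2, rounded up to 110 per arm, 220 in total, as stated.

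The target of 110 per arm therefore reproduces. The question is how patients reach the arms.

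**2. What the allocation text settles and what it leaves open.**

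| Element | Protocol |
|---|---|
| Source of numbers | Link with num=220, min=1, max=220, rnd=new |
| Rule | Even to intervention, odd to control |
| Stored, auditable list | None defined |
| Who draws and holds the numbers | Not stated |
| When an assignment is released | Not stated; only app training is placed after consent, and nothing places assignment after baseline |
| Safeguards | Study IDs and blinded analysts, both acting after enrolment |

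**3. What follows.** The text can be carried out in two ways.
- *Numbers drawn once and saved.* Someone without the list can guess the next arm about half the time; someone with the list knows it for certain. Concealment then depends wholly on custody, which the protocol does not address.
- *Link opened when needed.* Taking rnd=new at face value, each opening is a fresh draw. The chance of seeing a given parity at least once in k openings is 1 − (1/2)^k: 50%, 75% and 87.5% for k = 1, 2 and 3. Nothing in the protocol would record the discarded draws.

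**4. Arm size (secondary).** Assume the 220 integers are independent draws, so that the intervention count is Binomial(220, 0.5).
- SD = √(220 × 0.25) = 7.4.
- P(exactly 110/110) = 5.4%; central 95% range 95 to 125.
- P(arms differ by 20 or more) = 20.0%; by 30 or more = 5.0%.

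If instead each of 1 to 220 is used once, 110 of them are even and the split is exact.

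Power after 20% loss (110 × 0.8 = 88 per arm; 95/125 becomes 76/100), proportions without continuity correction:

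| Split | Proportions | Means |
|---|---|---|
| 110/110 | 83.1% | 81.1% |
| 95/125 | 82.1% to 82.8%, depending on which arm is larger | 80.4% |

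The cost is 83.1 − 82.1 = 1.0 point at most for proportions and 81.1 − 80.4 = 0.7 points for means.

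**5. Centres (secondary).** The protocol gives no centre sizes. Assume 36 patients (220 / 6 = 36.7, equal centres) or a small centre of 20. The probability of a 60/40 split or worse within the centre is:

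| Assumed centre size | Independent draws | Exact 110/110 overall |
|---|---|---|
| 36 | 24% | 20% |
| 20 | 50% | 48% |

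Even an exact overall split hardly protects balance within centres.

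**The case against.** Four stronger readings are tempting, and the document does not support them.

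- *A reader might infer that the recruiter holds the list.* The protocol does not say so. Drawing or keeping the numbers is not among that person's listed duties, and a third party could do it. Figure 1, cited under Design, and any other role descriptions are not in the text at hand. What stands is that no concealment is described while one unblinded person does all the recruiting.
- *A reader might infer that the open link exposes the sequence.* It does not: a link that redraws shows nobody the trial's list. Nor does it prove that the list is lost, since one draw could be saved. What stands is that no fixed list is defined and a redraw would go unseen.
- *A reader might infer that the method fails the stated 1:1 ratio.* Parity of independent draws is 1:1 in expectation. Only the planning figure of 110 per arm is not assured, and only if numbers can repeat. Asking for 220 numbers between 1 and 220 also fits an intention to use each once.
- *A reader might infer that missing stratification contradicts the plan.* The protocol never promises balance by centre, and simple randomisation of 220 individuals is a legitimate choice.

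It is also fair that clinicians refer patients first and that smartphone access (by patient or carer) is required in both arms. This narrows the room for selection but does not close it, because the team member still screens and takes consent.

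**Conclusion.** The concern holds as a gap in the stated method and must be fixed on concealment alone. The section that sets the allocation procedure names a redrawable source and a parity rule. It provides no fixed list, no custodian and no release point, and its two safeguards do not bear on selection at entry. Unblinded data collection and a self-reported primary outcome make the gap more serious here. No actual breach is shown, and the size of any bias cannot be derived from the document.

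The arm-size and centre points are secondary. The first rests on the assumption of independent draws and costs about 1 point of power or less. The second rests on assumed centre sizes and is a design weakness, not a contradiction.

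**What to change.** Replace the web-link rule with wording such as: *The allocation list is generated once, from a saved seed, by an investigator not involved in recruitment, using randomly varying permuted blocks. It is held in the study database or in sealed sequential envelopes. Each assignment is released only after eligibility, consent and baseline assessment have been recorded.*

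Varying the block size matters because the recruiter is unblinded and could otherwise work out the end of a block. Stratifying by metropolitan against rural (or by centre), with that factor in the primary model, is an optional low-cost addition.

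The cost is a few sentences in the protocol and a small amount of an existing investigator's time, with no extra patients or staff. Arms may still differ slightly from 110/110 because of incomplete blocks.

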**Outcome measures**

Outcome measures will be collected at 3, 6 and 9 months following the baseline data collection at recruitment.

Primary outcome

The primary outcome is the comparison of medication adherence between the two arms. Medication adherence will be measured by self-reported medication adherence tool Self-Efficacy for Appropriate Medication Use Scale (SEAMS) (Risser et al., 2007). This has been validated previously in other cardiac conditions such as coronary heart disease (Risser et al., 2007). This self-reported data will also be verified by the data collected from the intervention arm participants whose adherence rate has been captured by the data collected by the NPS MedicineWise application.

Secondary outcomes

i. composite outcome of death or hospital admission related to HF or not related to HF. All instances of hospitalization and death will be recorded and classification as to whether it was HF related or not will be done by experienced cardiologists

ii. health resource utilization (ie. Primary and secondary care contacts, social care contacts and relevant medication use)

iii. health related quality of life, assessed by EQ-5D-5L

iv. self-reported medication adherence

v. assessment of exercise tolerance (6 min walk test)

vi. psychological wellbeing (Depression anxiety and stress scales)

vii. self-care of HF index questionnaire

viii. medication knowledge

ix. acceptability, utility and engagement with the NPS MedicineWise application (Satisfaction survey)

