Data will be collected at each follow up on forms and then recorded as de-identified data only identified by the participant’s study number and stored electronically. At each follow up time point, 10 % of the data will be randomly selected for verification. In the event that discrepancies are identified, these will be verified using the original paper data sheet.

Participants’ names, addresses and smart phone numbers will be collected for the purpose of intervention delivery and participant interviews. All data collected from participants will otherwise be stored electronically as de-identified data which will be stored separately from identifiable data. All paper based data forms will be stored in locked filing cabinets within offices with restricted access. Electronic records will be stored in a secure server maintained by the University of South Australia. Data in the database will be backed up regularly. Access to all data will be restricted to the members of the research team and data will not be shared with any third parties.

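### The Protocol promises blinded data analysis without exception, but assigns the between-arm economic analysis to the unblinded person who recruits, trains and follows up participants

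*Protocol*

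**What the plan says.** The Protocol section Randomisation and blinding makes several linked statements. On participants: "Participants randomized in the control arm will be blinded to the intervention". On staff: "Due to the nature of the intervention, it will not be possible to blind the investigators". It then offers two measures against bias, first "However, to minimize bias, all participants will be allocated a study ID and all data will be collated using the study ID", and then "Analysis of the data will be conducted by blinded investigators". No analysis is exempted. The same section fixes how arms are assigned: "Participants allocated even numbers will be cases and participants allocated odd numbers will be controls", with numbers drawn from 1 to 220. Cases here means the intervention arm.

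The Design section adds that the researchers who collect data are not blinded. Trial data collection says that follow-up data are "recorded as de-identified data only identified by the participant’s study number".

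The role description at the end of the Protocol, after the reference list, covers daily running of the trial. One role recruits all participants, introduces the intervention arm to the app, liaises with the staff who deliver tiers 2, 3 and 3A, and covers "all follow ups with study participants at baseline, months 3, 6 and 9, and economic analysis".

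Economic evaluation and the Economic outcomes part of Data analysis describe a cost-utility analysis. It compares costs and EQ-5D-5L-based QALYs between arms from individual participants' data.

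For deaths and admissions, Outcome measures says that "classification as to whether it was HF related or not will be done by experienced cardiologists".

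**The concern.** The primary outcome is a self-report scale, and the staff who collect it know the arm. Masked analysis is one of the few safeguards left, so a reader will lean on the promise that it applies throughout. If it does not apply to the economic analysis, a stated property of the trial is wrong for the analysis that answers the first secondary aim.

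That analysis also leaves room for judgement. Unit costs may come from several kinds of source, and the one-way, multi-way and probabilistic sensitivity analyses are to be whatever is appropriate. An analyst who knows the arms can make those choices, even unintentionally, in the light of which arm they favour.

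A second question is whether masking is secure for the other analyses, since the rule linking number to arm is printed in the Protocol.

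**Working it through.** This is a consistency check between statements. The Protocol gives no figure to reproduce.

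**Step 1: scope of the promise.** The sentence in Randomisation and blinding refers to the data as a whole and carries no qualifier. It therefore covers the economic analysis.

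**Step 2: who has the economic analysis.** The role description lists it in the same sentence as recruitment, app training of the intervention arm, and every follow-up.

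**Step 3: does that person know the arms?** Yes, by three routes.
- Only intervention participants receive app training, so whoever gives it knows who they are.
- The follow-up interview differs by arm. Trial data collection puts the question about reminder aids to controls, and the end-of-study satisfaction survey goes to the intervention arm. The interviewer cannot conduct these without knowing the arm.
- The Design section states outright that data collectors are not blinded.

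**Step 4: is it a between-arm analysis?** Yes. Data analysis estimates the intervention's costs and outcomes relative to controls at participant level.

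**Result of steps 1 to 4.** The promise and the role assignment cannot both be true for the cost-utility analysis.

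**Step 5: does this reach the other analyses?** The text available does not name who analyses the primary scale or the other clinical outcomes. No contradiction is shown there.

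**Step 6: odd and even numbers.** The Protocol speaks of an allocated number, a study ID and a study number. It neither equates the study ID with the allocated number nor separates the two. The consequence depends on which holds:

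| Assumption | Records whose arm can be read from the ID |
|---|---|
| Study ID is the allocated number | 220 of 220 |
| Study ID is independent, and the allocated number is not in the analysis file | 0 of 220 |

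The documents do not settle where the trial lies. The control-only question, the satisfaction survey and the app data would also reveal the arm if they sat in the file used for between-arm tests. The Protocol does not say whether they do, and it describes the app data as a separate spreadsheet export.

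**Step 7: event classification.** Outcome measures is silent on whether the cardiologists are masked. Write H for HF-related events and N for other events in one arm. The composite counts both kinds. If k events are moved from one class to the other, the total is (H − k) + (N + k) = H + N. Only the HF-specific count changes, from H to H − k. The composite is unaffected for any k.

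**The case against.** The strongest reply is that this is a single loose phrase. Being in charge of activities need not mean running the analysis, and a statistical analysis plan may say who does and how the file is masked. Part of this stands: the contents of an analysis file are usually settled outside a protocol, and their absence here is no fault. The conflict itself remains, because both statements are in the Protocol. An analysis directed by someone who knows every arm does not meet an unqualified promise of blinded analysis either. The same role description ends with completing a masters degree, which suggests that the work is done by that person and not merely overseen.

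It can also be said that fixing model and code in advance does not mask someone who already knows the arms. That is right. It limits discretion but does not create blinding, so it is acceptable only if the Protocol stops calling the analysis blinded.

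Four stronger readings are tempting, and the documents support none of them.
- A reader might infer that blinded analysis is the only stated protection against bias. The same section also lists study IDs and blinding of control participants.
- A reader might infer that parity unmasks all 220 records. No statement makes the study ID the allocated number.
- A reader might infer that event adjudication is unblinded, or done by the referring site cardiologists. The Protocol says only that experienced cardiologists will do it. Investigator pages were removed from the text at hand, so who they are cannot be judged.
- A reader might infer that the primary analysis is unblinded. Nothing says so.

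**Conclusion.** The concern holds in a limited form. The blinded-analysis claim is untrue as written for one announced analysis, the cost-utility analysis. That analysis could draw on all 220 randomised participants and serves the first-listed secondary aim. This rests on reading the role description in its ordinary sense, as giving that person the economic analysis.

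For the primary and other clinical analyses, masking is at risk but not shown to be broken. The risk turns on whether the study ID is independent of the odd/even number and whether arm-specific fields are kept out of the comparison file.

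The silence on masking of the classifying cardiologists is a lesser point, confined to HF-specific counts.

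The size of any resulting bias in cost per QALY cannot be computed from the documents. The correction is worth making because a stated safeguard is false for a named analysis and the remedy is cheap.

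**What to change.** **Randomisation and blinding, and the role description.** Choose one of two courses and make both places agree.
- Have a masked analyst who is already planned run the between-arm economic comparison on data coded A/B. Costs that arise only from delivering the app programme would then be added after the code is broken, from a costing fixed beforehand.
- Otherwise, state that the economic analysis is not blinded, and fix its model, unit costs, sensitivity analyses and code before outcome data are analysed.

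**Randomisation and blinding.** State that study IDs are independent of the odd/even allocation number. State also that the file for between-arm analysis carries a neutral A/B code, with control-only and intervention-only fields withheld until the comparisons are fixed.

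**Outcome measures (lesser point).** State whether the cardiologists are masked. Those already planned can classify HF-relatedness from records with references to arm and app removed.

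**Cost.** A short amendment, some data handling and some redaction of records, with no new staff. The second course also means a narrower blinding claim.
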